### Participant timeline {13}

The participant timeline is shown in Table 2. Nonblinded investigators will obtain informed consent for surgery and inclusion in the clinical trial after admission 1–2 days before surgery. We will confirm and record each patient’s medical history, allergies, and physical examination results. After their written informed consent has been obtained, patients eligible for this trial will be randomized into two groups before surgery. The observation period will be approximately 1 year after surgery. The 1-year follow-up visit is defined as a follow-up visit up to 15 months after surgery. Table 2 shows a summary of the schedule and the data collected for this trial.

**Table 2 Tab2:** Schedule and data collection of this trial

	Study period						
	Before allocation	After allocation			Follow-up		
**Timepoint**	1–2 days	Surgery	POD1	POD3	POD4–29	POD30	9–15 months
**Screening**	X						
Eligibility screen	X						
Informed consent	X						
Randomization		X					
**Interventions**		X					
Intervention A		X					
Intervention B		X					
**Assessments**							
Demographic data	X						
Medical history	X						
Physical examination	X						
Blood sample	X		X	X			
Type of operation		X					
Time of operation		X					
Wound classification		X					
Estimated blood loss		X					
Blood transfusion		X					
Stoma creation		X					
Documentation of wound complications			X	X	X	X	
Wound swab microbiology			X	X	X	X	
Documentation of reoperation			X	X	X	X	
Documentation of AE			X	X	X	X	
Duration of hospital stay						X	
Computed tomography							X
Documentation of incisional hernia							X

*AE*, adverse effect

### Sample size {14}

A retrospective cohort of patients who underwent gastrointestinal surgery and MAWI closure (in which the peritoneum and fascia were sutured together using interrupted sutures with 1-PDS plus, with subcutaneous interrupted sutures then used for skin closure using 4–0 PDS) at our department from June 2019 to December 2020 was analyzed. The incidence rates of each complication were as follows: incisional SSI (7.6%), hematoma (5.1%), 5.9% seroma (5.9%), superficial dehiscence (1.4%), total dehiscence (0%), and IH at approximately 1 year after surgery (16.8%). When a patient developed more than 2 wound complications, the number of patients who developed wound complications was assumed to be one. In total, the incidence of wound complications was 29.2%. In this trial, we hypothesized that midline abdominal wall incision closure with continuous suturing of the fascia using a single-layer aponeurotic technique and continuous suturing of the subcuticular tissue would achieve a 50% reduction in the incidence of wound complications. The expected wound complication rates of the study and control groups were 14.6% and 29.2%, respectively. Power and Sample Size Calculation version 3.1.6 was used for sample size estimation [21]. With a two-sided alpha level of 0.05, it is estimated that a total of 250 patients will be needed for the trial to have 80% power to detect superiority in the reduction of the frequency of wound complications. Two percent of cases are expected to be excluded after allocation, and 10% of cases are expected to drop out during the postoperative follow-up period. Thus, the total target number of cases is set at 284 (Fig. 1).

**Fig. 1 Fig1:**
[figure not shown]
CONSORT flow chart

### Recruitment {15}

This trial was approved by our institutional review board on June 30, 2022, and is registered in the University Hospital Medical Information Network Clinical Trial Registry (part of the WHO International Clinical Trial Registry Platform) under the identification number UMIN-CTR000048442. Patients who receive elective gastroenterological surgery will be considered candidates for trial enrollment in concordance with the inclusion and exclusion criteria. Informed consent will be obtained from all participants by investigators. We are confident that we can enroll a sufficient number of eligible patients, as our institution conducts over 300 elective gastroenterological surgeries with clean-contaminated wounds annually.

## Assignment of interventions: allocation

### Sequence generation {16a}

Participants will be registered, randomized, and allocated by nonblinded investigators. Participants’ data will be password-protected and will only be accessible by investigators. All access to the secure separate database will be monitored and logged. Permuted-block randomization with an allocation ratio of 1:1 and blocking will be used. The randomization will be stratified by sex, surgical organ (upper gastrointestine, small bowel, colorectum, hepatobiliary–pancreas, and others), and surgical approach (laparotomy or laparoscopy).

### Concealment mechanism {16b}

A web-based block randomization system (Research Electronic Data Capture [REDCap]) will be used to generate the randomization sequence [22]. Both the randomization methodology and the allocation sequence will be concealed from both the assessor and the participants.

### Implementation {16c}

An independent investigator will generate a stratified randomization list for the allocation sequence. Investigators will enroll and assign participants to interventions.

## Assignment of interventions: blinding

### Who will be blinded {17a}

Patients will be blinded to their assigned group. However, the operating surgeons cannot be blinded. The assessors will be blinded, as they will not be in the operating room and cannot access the randomization results. The data on wound complications and analyses will be entered by blinded investigators. The biostatistician will be blinded.

### Procedure for unblinding if needed {17b}

As investigators are aware of the participant allocation, unblinding will not be needed.

## Data collection and management

### Plans to promote participant retention and complete follow-up {18b}

Participants are patients who require regular follow-up and are scheduled to undergo computed tomography 1 year after surgery. We expect that participants will be available for follow-up due to concerns about disease recurrence.

### Data management {19}

The study will be conducted according to good clinical practice standards and legal regulations. Prior to inclusion, patients will be informed that any patient-related data and materials will be appropriately pseudonymized and that these data may be used for analytical and publication purposes. All information required by the study protocol and collected during this trial will be entered in the electronic case report form (CRF; encrypted Excel database) by investigators. The data entry module contains an online range and logical checks. All data will be collected by the investigators in an anonymous and encrypted database. The confidentiality of the participants will be maintained at all times. The investigator will maintain all study-related information, including medical records, CRFs, written informed consent documents, and other pertinent data, for 5 years after trial termination.

### Confidentiality {27}

The investigators will obtain the participants’ information from medical records and collect the information in a password-protected file in the hospital database. The participants’ hospital identification will be anonymized. Datasets will only include summary data, which cannot identify individual participants. These will be presented in the manuscript.

### Plans for collection, laboratory evaluation, and storage of biological specimens for genetic or molecular analysis in this trial/future use {33}

Not applicable as no biological specimens will be collected in this study.

## Statistical methods

### Statistical methods for primary and secondary outcomes {20a}

All analyses will be performed after the termination of the main part of the trial, that is, after the last 1-year follow-up visit has taken place. We will perform the primary analyses using the full analysis set, from which patients who do not undergo surgery or who withdraw their consent before the assessment of the primary endpoint are excluded (modified intention-to-treat set). In addition, we will repeat the analyses in the per-protocol set, further excluding patients with major protocol deviations. Student’s *t* test or the Mann–Whitney *U* test will be used to compare continuous variables with a normal or nonnormal distribution. The *χ*^2^ test or Fisher’s exact test will be used to compare categorical variables between the study group and the control group. *P* values of < 0.05 were considered to indicate statistical significance. All statistical analyses will be conducted using EZR [23].

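### Randomization is stratified by sex, organ and approach, but the stated primary test ignores the strata and is left as chi-square or Fisher, while the 250 patients give 80% power only for the uncorrected chi-square

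*Protocol article*

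**What the plan says.** - **Randomization** (Protocol article, Sequence generation {16a}): 1:1 permuted blocks. "The randomization will be stratified by sex, surgical organ" and by surgical approach. With 2 sexes, 5 organ groups and 2 approaches there are 20 strata. The block size is not given.
- **Primary comparison** (Statistical methods for primary and secondary outcomes {20a}): the primary outcome, any wound complication, is binary. The section offers a chi-square test or Fisher's: "exact test will be used to compare categorical variables between the study group and the control group". It names no stratified or adjusted analysis, gives no rule for choosing between the two tests, and does not say whether the chi-square is continuity-corrected.
- **Subgroups** ({20b}): approach reappears, but only as a subgroup factor.
- **Sample size** ({14}): "The expected wound complication rates of the study and control groups were 14.6% and 29.2%, respectively". "With a two-sided alpha level of 0.05", "a total of 250 patients will be needed for the trial to have 80% power to detect superiority". Losses: "Two percent of cases are expected to be excluded after allocation, and 10% of cases are expected to drop out". Hence "the total target number of cases is set at 284".

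**The concern.** Two separate things are at issue.

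1. **Strata left out of the test.** Blocking within prognostic strata makes the arms more alike than simple randomization would. A test that ignores the strata uses a variance that is too large. It is then conservative and gives up some of the precision that the stratification was meant to buy.
2. **Two tests, one sample size.** The planned number of patients corresponds to one particular test, but the analysis section permits others with a lower rejection rate. With no selection rule, a borderline result could be significant under one permitted test and not under another.

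At stake are a few points of power and a clear, prespecified primary P value. The validity of a positive result is not at stake.

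**Working it through.** **Inputs from the article.** Control rate p1 = 0.292, study rate p2 = 0.146, difference d = 0.146, two-sided alpha 0.05, power 80%, 250 evaluable (125 per arm), losses 2% and 10%.

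**Step 1. Reproduce the plan's figures.** The pooled-variance formula without continuity correction is

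n = [1.960·√(2·p̄·(1−p̄)) + 0.842·√(p1(1−p1) + p2(1−p2))]² / d², with p̄ = (0.292 + 0.146)/2 = 0.219.

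- First term: 1.960 × √0.3421 = 1.146.
- Second term: 0.842 × √0.3314 = 0.485.
- n = (1.631)² / 0.0213 = 124.8, so 125 per arm and **250 in total**, as stated.
- Inflation: 250/0.88 = 284.1, or 250/(0.98 × 0.90) = 283.4. Both agree with **284**.

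The continuity-corrected version, (n/4)·[1 + √(1 + 4/(n·d))]², gives 138.1, so 139 per arm or 278 in total. It does not match the plan. The sample size therefore assumes the uncorrected chi-square.

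**Step 2. Exact power of the permitted tests**, by full enumeration of the two binomials:

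| Test | Power, 125 per arm | Type I error, both arms 29.2% | Type I error, both arms 21.9% |
|---|---|---|---|
| Chi-square, uncorrected | 80.3% | 5.0% | 4.9% |
| Chi-square, continuity-corrected | 76.1% | 3.6% | 3.5% |
| Fisher | 76.1% | 3.6% | 3.5% |

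- The gap is 80.3 − 76.1 = 4.2 points. In that share of trials under the planning rates, the uncorrected chi-square is significant and Fisher is not.
- Exact Fisher power first reaches 80% at 137 per arm (80.3%; at 136 it is 79.9%). That is 274 evaluable, or 274/0.88 = 311.4 randomized.
- If all 284 were evaluable (142 per arm), Fisher would have 82.0%.

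**Step 3. Effect of ignoring the strata.** The article gives no stratum-specific risks, stratum shares or block size, so these are assumptions. The simulations use 20 strata, N = 250, blocks of 4, and marginal rates held at 29.2% and 14.6%. The 20,000-run set uses stratum shares of sex 60/40, organ 25/5/45/20/5 and approach 30/70. The chi-square is uncorrected.

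| Control risk across strata | Runs | Power, unstratified | Power, Cochran-Mantel-Haenszel | Type I error, unstratified |
|---|---|---|---|---|
| Equal in all strata | 20,000 | 80.3% | 79.7% | 5.3% |
| Equal in all strata | 8,000 | 80.7% | 80.2% | 4.9% |
| 15–46% | 8,000 | 80.7% | 80.8% | 4.8% |
| 17–48% | 20,000 | 80.8% | 80.7% | 5.0% |
| 13–55% | 5,000 | 80.5% | 81.8% | not reported |
| 7–63% | 8,000 | 81.6% | 83.7% | 3.9% |
| 9–66% | 20,000 | 81.8% | 83.8% | 4.0% |
| 8–69% | 5,000 | 81.1% | 84.5% | 3.5% |

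Simulation error on the type I rates is about 0.15 points at 20,000 runs. In that set the Cochran-Mantel-Haenszel test had type I error of 5.2%, 5.5% and 5.2% for equal, moderate and strong strata.

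The change in power from stratifying therefore runs from about −0.6 points (strata not prognostic), through about nil (moderate) and 1.3 points (13–55%), to 2.0, 2.1 and 3.4 points (strong).

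**The case against.** **The strata may not matter.** The Background names obesity, smoking, old age and SSI itself as risk factors for incisional hernia. None of these is a stratification factor. Only approach has support, through the statement there that minimally invasive surgery reduces incisional hernia. A gain of 2 points or more needs roughly a seven- to nine-fold spread in control risk across strata, and nothing in the article shows one. This stands, and it limits how large the effect can be said to be.

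**The planned chi-square keeps its promise.** In every scenario the uncorrected chi-square has at least the stated 80% power. This also stands. A reader might infer that the plan wastes power outright or misstates its error rate. The documents do not support either inference. The loss depends on stratum risks that they do not give, and any departure in the error rate is in the conservative direction.

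**Fisher is unlikely to be used for the composite.** The sentence covers all categorical variables, including rare ones such as superficial dehiscence (1.4% in the retrospective cohort). Expected events in the composite are 125 × 0.146 = 18 and 125 × 0.292 = 37 per arm, so there is no small-count reason for Fisher, and the 250 points to the uncorrected chi-square. A reader might infer that the trial is underpowered. It is so only if Fisher or a continuity correction is actually chosen. What remains is that the text permits that choice and states no rule.

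**Twenty strata are many for 250 patients.** The average is 250/20 = 12.5 per stratum. Under the assumed shares the smallest cell expects 250 × 0.4 × 0.05 × 0.3 = 1.5 patients. This is fair, and it is why the pooling must be fixed in advance.

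**A statistical analysis plan may settle it.** Possibly, but the article does not leave the primary test unmentioned. It states one, and that test does not follow the stated randomization.

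**Conclusion.** The point holds in a limited form. The stated primary comparison ignores the factors used for randomization. If those factors are strongly prognostic, the unstratified test is conservative (type I error of about 3.5% to 4%) and a stratified test would gain about 2 to 4 points of power. With weak or moderate strata the gain is about nil. These sizes rest on assumed stratum risks, shares and block size.

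Independently of stratification, the 250 evaluable patients deliver 80% power only with the uncorrected chi-square. Either of the other readings of the analysis sentence gives 76.1%. That figure rests only on the article's own planning rates.

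This is worth changing because it is nearly free and all analyses are deferred until after the last 1-year visit. It does not undermine the design or the sample size.

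**What to change.** Before any outcome analysis, state one primary analysis:

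- **Primary:** Cochran-Mantel-Haenszel test without continuity correction, stratified by sex, organ and approach. Specify in advance how sparse organ levels are pooled (for example small bowel with others, if their counts are low), deciding on numbers of patients and without sight of outcome by arm. Report the stratified risk difference with its 95% CI.
- **Sensitivity:** the unstratified, uncorrected chi-square on which the sample size is based.
- **Not for the primary outcome:** Fisher's test or a continuity correction. Fisher can remain for rare individual components.

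The cost is protocol or analysis-plan wording and slightly more analysis work. No further patients or data are needed, since the stratification factors are already recorded at randomization. The downside is a loss of about half a point of power (0.5 and 0.6 points in the simulations) if the strata prove not to be prognostic.

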## Introduction

### Background and rationale {6a, 6b}

Wound complications are among the most common morbidities for patients after gastroenterological surgery [1–4]. Short-term postoperative wound complications include incisional surgical site infection (SSI) [1, 2], hematoma, seroma, and wound dehiscence. Incisional hernia (IH) accounts for the majority of long-term postoperative wound complications [3, 4]. Both short-term and long-term wound complications are associated with a decreased quality of life, increased risks of morbidity and mortality, and dramatically increased medical costs [1–5]. Obesity, smoking, and old age are well-known risk factors for IH and highly overlap with the risk factors for SSI and wound dehiscence. Furthermore, SSI itself is an important risk factor for IH, and wound dehiscence may predict IH [6]. Thus, the pathogenesis and development of all wound complications may be correlated with each other, and a comprehensive approach to reduce the overall incidence of wound complications should be developed.

The wound closure technique that is used to close an abdominal wall incision is an important determinant of the risk of developing wound complications, especially in IH [3, 4]. The European Hernia Society proposed guidelines on the closure of abdominal wall incisions in 2015 [3], and it was recently updated by the European and American Society in 2022 [4]. For closure of the fascia, they recommend the combined use of a continuous small-bite suturing technique with slow absorbable sutures to reduce the risk of IH [3, 4].

Although the guidelines recommend the continuous suture technique, there has been no high-quality evidence suggesting the superiority of the continuous suture technique to the intermittent suture technique for the prevention of wound complications. Reliable recent meta-analyses that compared the interrupted and continuous suture techniques showed that there was no difference in the incidence of HH, wound dehiscence, or SSI [7, 8]. These meta-analyses included many smaller and older studies of low-certainty evidence; therefore, the evidence is of poor quality [7, 8]. Accordingly, for the establishment of high-quality evidence of wound closure techniques, further studies should be conducted to compare the impact of interrupted and continuous suture techniques in the prevention of wound complications.

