### Additional consent provisions for collection and use of participant data and biological specimens {26b}

Patient characteristics, such as sex, age, body mass index, serum albumin level, comorbidities, American Society of Anesthesiologists-physical status classification and preoperative treatment, will be collected. In addition, surgical data, such as the surgical procedure, operative time, estimated blood loss, wound classification, and length of postoperative hospital stay, will be collected. Additional biological specimens will not be collected for this trial. The investigators do not expect to conduct ancillary studies requiring the use of participant data that is collected in this study.

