### Outcomes {12, 18a}

#### Primary outcome

The primary outcome is the incidence of wound complications, including incisional SSI, hemorrhage, seroma, and wound dehiscence within 30 days after surgery and IH at approximately 1 year after surgery. Nonblinded investigators will check the surgical wound and describe the medical records during hospitalization. If wound complications are suspected based on the clinical findings, nonblinded investigators will record the treatment details in the medical record. After discharge, participants will be referred to the outpatient department approximately 30 days after surgery. Participants will be recommended to contact us and visit the outpatient department soon if they experience any symptoms suggesting wound complications. Nonblinded investigators will examine the patients in the same way as during hospitalization. One year after surgery, participants will be referred to the outpatient department, and the incidence of incisional hernia will be assessed with a physical examination by nonblinded investigators and computed tomography (CT) of the abdomen. The blinded assessors will determine the presence or absence of wound complications according to the clinical records.

Incisional SSI is defined according to the standard criteria devised by the CDC [18]. Incisional SSI includes superficial and deep incisional SSI that develops during the first 30 days after surgery. Superficial incisional SSI involves the skin or subcutaneous tissue at the incision site, and deep incisional SSI affects more internal structures of the abdominal layer (such as the fascia or muscle). Wound hemorrhage is defined as superficial postoperative wound bleeding or subcutaneous hematoma. Seroma is defined as a collection of serous fluid in the subcutaneous space, detected either clinically or by imaging. Wound dehiscence includes superficial dehiscence and total dehiscence. Superficial dehiscence is defined as skin-only dehiscence. Total dehiscence is defined as a dehiscence of the entire abdominal wall. IH is defined as any abdominal wall gap with or without a bulge in the area of a postoperative scar that is perceptible or palpable by clinical examination or imaging according to the European Hernia Society guidelines [19].

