### Method for additional analyses (e.g., subgroup analyses) {20b}

Subgroup analyses will be performed for the surgical approach (laparotomy or laparoscopy). *P* values of < 0.05 will be considered statistically significant.

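### The primary test is unadjusted and leaves out BMI and age, which the protocol collects and treats as risk factors; the test is valid, but some precision and protection against chance imbalance are given up (minor).

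*Protocol article*

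**What the plan says.** **Outcome and test.** The primary outcome is a yes/no composite: "The primary outcome is the incidence of wound complications, including incisional SSI, hemorrhage, seroma, and wound dehiscence within 30 days after surgery", plus incisional hernia at about one year. Statistical methods {20a} assigns categorical outcomes a chi-square or Fisher's exact test, which "will be used to compare categorical variables between the study group and the control group". No regression or stratified comparison is stated. The only additional analysis is by operative approach: "Subgroup analyses will be performed for the surgical approach (laparotomy or laparoscopy").

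**Risk factors.** Background and rationale {6a, 6b} states: "Obesity, smoking, and old age are well-known risk factors for IH and highly overlap with the risk factors for SSI and wound dehiscence".

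**Data collected.** Section {26b} lists "Patient characteristics, such as sex, age, body mass index, serum albumin level, comorbidities" and further items. Age and BMI are therefore available for every patient before surgery. Smoking is not listed by name there.

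**Randomization.** Sequence generation {16a}: "The randomization will be stratified by sex, surgical organ" and operative approach. BMI and age are not among the factors.

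**Sample size {14}.** "The expected wound complication rates of the study and control groups were 14.6% and 29.2%, respectively". "With a two-sided alpha level of 0.05, it is estimated that a total of 250 patients will be needed" for 80% power, and the target is 284 after losses.

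**The concern.** The protocol singles out two measurable patient characteristics as predictors of the outcome and collects both, but uses them in neither the allocation nor the primary comparison. Adjusting for a prognostic baseline value removes outcome variation that has nothing to do with treatment. It also corrects the estimate for whatever difference in that value chance leaves between the arms.

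Two things are at stake. The first is a little power in a trial planned at just 80%. The second is the credibility of a borderline single-centre result if one arm turns out heavier or older, since an adjustment chosen after seeing such an imbalance carries less weight than one fixed beforehand.

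This point is separate from adjusting for the stratification factors, because BMI and age are not among them.

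**Working it through.** **1. The plan's own figure.** Inputs from Sample size {14}: p1 = 0.292, p2 = 0.146, two-sided alpha 0.05, power 80%. The mean rate is 0.219.

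n per arm = [1.96·√(2·0.219·0.781) + 0.842·√(0.292·0.708 + 0.146·0.854)]² / 0.146² = (1.146 + 0.485)² / 0.0213 ≈ 124.8, rounded up to 125, so 250 in total.

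This matches the stated number. With a continuity correction the result is 139 per arm, or 278, which does not match. Power at 125 per arm is 80.1%. For losses, 250/(0.98·0.90) = 283.4, rounded up to 284. The stated 80% power is therefore the power of the unadjusted test.

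**2. Gain from adjustment, like for like.** The documents give no odds ratio for BMI or age, so these are assumed, per standard deviation. Trials of 125 per arm were simulated with marginal rates held at 29.2% and 14.6%. The same test (likelihood ratio for arm) was used with and without the two covariates, so that a change of test does not pass for a gain from adjustment. Two separate runs of 4,000 trials per scenario gave:

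| Assumed OR per SD (BMI / age) | Run 1: unadjusted → adjusted power | Run 1 gain (points) | Run 2 gain (points) |
|---|---|---|---|
| 1.35 / 1.22 | 80.8% → 81.4% | 0.6 | about 0.3 |
| 1.65 / 1.35 | 80.1% → 82.7% | 2.6 | 1.8 |
| 2.0 / 1.5 | 81.0% → 84.6% | 3.6 | 3.9 |

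The simulation error of each power figure is √(0.8·0.2/4000) ≈ 0.6 points, so the two runs agree.

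**3. Variance and type I error.** A further simulation (3,000 trials per scenario) gave both covariates the same odds ratio. It compared the chi-square test with the Wald test for arm in the adjusted logistic model.

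| OR per SD, both covariates | Power, unadjusted / adjusted | Variance of risk difference, adjusted ÷ unadjusted | Type I error, unadjusted / adjusted |
|---|---|---|---|
| 1.0 | 79.7% / 79.5% | 1.01 | 5.3% / 5.6% |
| 1.25 | 82.3% / 82.9% | 1.00 | 5.1% / 5.4% |
| 1.5 | 80.9% / 82.3% | 0.95 | 4.6% / 4.4% |
| 2.0 | 80.8% / 85.4% | 0.89 | 4.9% / 5.7% |

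If the covariates are not prognostic, the loss is 0.2 points. The 4.6-point difference in the last row is not like for like, because the two columns use different tests, and it needs both covariates at 2.0.

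**4. Chance imbalance.** The standardised difference between arms in an unstratified covariate has a chance SD of √(2/125) = 0.126, so a 2-SD imbalance is about 0.25 SD. The approximate shift in the risk difference is 0.219·0.781·0.25·ln(OR). This gives 1.0, 1.7 and 3.0 percentage points at OR 1.25, 1.5 and 2.0, against a target difference of 14.6 points.

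**5. How many parameters the data can carry.** Expected events are 125·0.292 + 125·0.146 = 36.5 + 18.3 ≈ 55. Arm, BMI and age are 3 parameters, about 18 events each. Adding sex (1), five organ classes (4) and approach (1) makes 9, about 6 events each.

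**The case against.** The strongest reply is that nothing here is an error. An unadjusted chi-square test in a 1:1 randomized trial is valid, its type I error already allows for chance imbalance, and the sample size was built on it. All of that stands.

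A reader might infer that the missing adjustment biases the result or leaves the trial underpowered. The documents support neither reading. The unadjusted comparison is unbiased on average under randomization, its simulated type I error is 4.6% to 5.3%, and its power under the planning assumptions is the stated 80%.

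The benefit is also small, and its size rests on assumed odds ratios. Section {6a, 6b} ties the risk factors to hernia, infection and dehiscence. It does not tie them to hematoma or seroma, which were 5.1% and 5.9% in the planning cohort, so their effect on the composite may be diluted. This stands, and it is why the point is minor.

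A model that adds every stratification level to BMI and age is stretched on about 55 events. Under an assumed organ mix its null rejection rate was 5.5% to 5.6%, against 4.7% to 5.0% for the unadjusted test. This stands too, and it limits the fix.

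Finally, covariates are often left to the analysis plan, which is not shown and might add an adjusted analysis. This carries less weight: the article does not leave the primary comparison open but names an unadjusted test for it.

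**Conclusion.** The point holds as an efficiency matter and is minor. The protocol fixes an unadjusted primary comparison while collecting two baseline values that it regards as risk factors for much of the composite. For assumed odds ratios between about 1.25 and 2.0 per SD, pre-specified adjustment would add about 0 to 4 power points like for like. It would cut the variance of the risk difference by about 0 to 11%, the upper end requiring both covariates at 2.0. Type I error stays near 5%, and the loss is negligible if the covariates turn out not to be prognostic. A 2-SD chance imbalance in one covariate would move the estimate by roughly 1 to 3 points: too little to overturn a true 14.6-point effect, but enough to matter near the significance boundary.

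These sizes rest on assumed prognostic strengths, independent covariates, the planned event rates and 250 evaluable patients. No validity or power failure follows from them.

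**What to change.** Before unblinding, state the primary analysis as a logistic model with arm, continuous BMI and continuous age, with the form of each covariate fixed in advance. Report the standardised (marginal) risk difference with its 95% CI as the effect estimate, and keep the chi-square or Fisher test as a supportive analysis.

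If sex, organ and approach are also included, specify beforehand how sparse organ levels will be merged, so that the number of parameters stays small relative to about 55 events. Smoking could be considered under the same limit, but only if the medical history already records it.

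The cost is a wording change by amendment, with the ethics review and registry update that the protocol already provides for, and a few lines of code. No new data or patients are needed. The downside is that a model-based estimate is slightly less simple to present than two percentages.
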